## Abstract

**Introduction:**

Acute pancreatitis is an inflammatory disease of the pancreas with high risk of developing multiorgan failure and death. There are no effective pharmacological interventions used in current clinical practice. Maintaining fluid and electrolyte balance is the mainstay of supportive management. Goal-directed fluid therapy (GDFT) has been shown to decrease morbidity and mortality in surgical conditions with systemic inflammatory response. There is currently no randomised controlled trial (RCT) investigating the role of GDFT based on cardiac output parameters in patients with acute pancreatitis in the ward setting. A feasibility trial was designed to determine patient and clinician support for recruitment into an RCT of ward-based GDFT in acute pancreatitis, adherence to a GDFT protocol, safety, participant withdrawal, and to determine appropriate endpoints for a subsequent larger trial to evaluate efficacy.

**Methods and analysis:**

The GDFT in Acute Pancreatitis trial is a prospective two-centre feasibility RCT. Eligible adults admitted with new onset of acute pancreatitis will be enrolled and randomised into ward-based GDFT (n=25) or standard fluid therapy (n=25) within 6 hours from the diagnosis and continuing for the following 48 hours. Cardiac output parameters will be monitored with a non-invasive device (Cheetah NICOM; Cheetah Medical). The intervention group will consist of a protocolised GDFT approach consisting of stroke volume optimisation with crystalloid fluid boluses, while the control group will receive standard care fluid therapy as advised by the clinical team. The primary endpoint is feasibility. Secondary endpoints will include safety of the intervention, complications, mortality, admission to intensive care unit, cost and quality of life.

**Ethics and dissemination:**

Ethics approval was granted by the London Central Research Ethics Committee (17/LO/1235, project ID: 221872). The results of this trial will be presented to international conference with interest in general surgery and acute care and published in a peer-reviewed journal.

**Trial registration number:**

ISRCTN36077283.

Strengths and limitations of this studyAdequate fluid therapy is a major determinant of outcomes in acute pancreatitis, however, there is no consensus on the rate, type and volume of fluids to be administered. Goal-directed fluid therapy (GDFT) based on stroke volume (SV) optimisation has been used after major surgery with a reduction in complications, however, delivering this intervention on the ward has been challenging without invasive monitoring.Novel development of non-invasive cardiac output monitoring (NICOM) technologies allows GDFT to be delivered in the ward based on haemodynamic parameters. This trial is the first GDFT randomised trial in acute pancreatitis using NICOM in the ward setting for SV optimisation.The golden period for intervention in acute pancreatitis is in the early phase of disease to prevent progression to severe inflammatory processes and complications. A major challenge in this trial is recruitment and delivering the intervention in the early hours of unplanned admission which is shared across trials in emergency care.

## Introduction

Acute pancreatitis is a sudden onset inflammatory process of the pancreas, with variable involvement of local or remote organ systems. The annual incidence of acute pancreatitis in the UK is approximately 30 per 100 000 of the population.^1^ This equates to approximately 18 000 people developing acute pancreatitis every year in the UK.^1^ There has been an increase in the incidence of pancreatitis in the last two decades.^2^ Gallstones and excessive alcohol are the two main causes for acute pancreatitis in the UK.^3^ Increasing age, male gender and lower socioeconomic class are associated with a higher incidence of acute pancreatitis.^1^

The clinical manifestation of acute pancreatitis is believed to be caused by activation of inflammatory pathways either directly by the pathologic insult or indirectly by activation of trypsin, a protease which can break down the pancreas.^4^ The average 60-day mortality associated with acute pancreatitis is 6.4%.^1^ Deaths occur as a result of a massive fluid extravasation from the inflamed pancreas combined with a severe systemic inflammatory response in the early stage and mainly from local complications in the late stage.^5^ The systemic complications occurring in the early phase result in poor oxygen delivery to the tissues and include worsening of pre-existing illnesses such as heart or chronic lung disease. Local complications which occur in the later phase include pancreatic pseudocysts, infected collections and pancreatic necrosis. These early and late complications are the major causes of the mortality associated with acute pancreatitis.^6 7^ They are also largely responsible for the decreased health-related quality of life (HRQoL) and loss of work days following acute pancreatitis.^8^ Thus, acute pancreatitis has a major effect on UK society with its complications having a significant impact on patients, their next of kin and their employers.

Various pharmacological interventions have been evaluated in acute pancreatitis, but none are in current clinical practice.^9^ Supportive management in terms of maintenance of fluid and electrolyte balance remains the mainstay in the treatment of acute pancreatitis. Despite the key importance of fluid therapy, a recent systematic review has highlighted that there is a lack of information on the optimal fluid therapy in acute pancreatitis.^9 10^ There has also been a decline in research in treatments for acute pancreatitis in general.^11^

The clinical presentation of acute pancreatitis varies from mild to severe life-threatening conditions. There is some evidence for aggressive fluid therapy with Hartmann’s solution in those with severe disease. However, the rate and volume of fluid therapy is still debated for those with mild or moderate disease. Hence, high-quality randomised controlled trials (RCT) in fluid therapy for acute pancreatitis are necessary.

Goal-directed fluid therapy (GDFT) is a complex intervention in which intravenous fluid is given to optimise haemodynamic variables. This is achieved by stroke volume (SV) optimisation using a cardiac output (CO) monitor. RCTs have shown that GDFT decreases complications and mortality in other situations associated with a systemic inflammatory response.^12 13^ Most of these trials however involved cardiac output monitoring for GDFT during surgery or in the intensive therapy unit (ITU) and not in a ward-based setting. For GDFT to be beneficial in acute pancreatitis, which involves a cascade of inflammatory events, therapy is likely to be most beneficial if commenced at the earliest opportunity to intervene following the onset of pancreatitis which would equate with the time of admission to hospital. There has been one RCT on ward-based GDFT in patients with acute pancreatitis comparing the effect of GDFT with lactated ringers to normal saline on inflammatory response.^14^ However, the trial was based on optimisation of blood urea nitrogen and not cardiac output parameters and failed to show a reduction in the inflammatory response or improved clinical outcomes. While other endpoints such as heart rate, urine output, haematocrit levels and central venous pressures have been suggested for fluid therapy in acute pancreatitis, it is the optimisation of intravascular volume with fluid therapy guided by cardiac output measures that has been previously shown to be effective in decreasing complications and mortality in major surgery.^15 16^ There is currently no RCT investigating the role of ward-based GDFT using cardiac output parameters as target in patients with acute pancreatitis.

With the development of non-invasive cardiac output monitors such as Cheetah NICOM (Cheetah Medical, Maidenhead, Berkshire, UK), it is possible to measure the cardiac output in a ward setting.^17^ Ward-based GDFT has the potential to decrease the early inflammatory response and hence complications related to acute pancreatitis which might result in decreased mortality and improved HRQoL. Reduced inflammation would also lead to a reduced intensive care unit (ICU) and hospital stay providing significant cost savings to the National Health Service (NHS), employers and care providers. This two-centre RCT will aim to assess the feasibility of guiding the initial 48 hours of intravenous fluid administration in patients with acute pancreatitis using ward-based GDFT.

## Methods

### Study design and setting

The GDFT in Acute Pancreatitis (GAP) trial has been designed in accordance with the Standard Protocol Items: Recommendations for Interventional Trials guidelines as a two-centre feasibility RCT.^18^ The study will primarily investigate the ability to recruit patients at the selected sites to a feasibility RCT of ward-based GDFT versus standard fluid therapy in patients with acute pancreatitis, the rate of withdrawal from GDFT protocol and the reasons for withdrawal from GDFT protocol. We will also assess the safety and practicality of ward-based GDFT and collect outcome measures which can be evaluated as endpoints for a subsequent multicentre study on efficacy. Indicative costs will be collected to inform a subsequent cost-effectiveness study. The trial outline is illustrated in figure 1 and the schedule of enrolment, interventions and assessments is shown in table 1.

**Figure 1 F1:**
[figure not shown]
Trial flow diagram. Patients are screened by the medical and surgical team in the emergency department for eligibility and referred for consent and registration. The trial nurse or surgical team provide trial patient information sheets (abbreviated and full versions) and gain informed consent. Trial nurses then randomise the patient to either GDFT or standard care and commence NICOM monitoring for 48 hours. Follow-up will be at the point of discharge, 30 and 90 days. GDFT, goal-directed fluid therapy; GP, general practitioner; HRQoL, health-related quality of life; NICOM, non-invasive cardiac output monitoring.

**Table 1 T1:** Schedule of enrolment, interventions and assessments

Procedures	Enrolment	Allocation	Postallocation								Closeout
Time point	−t0	0	0 hour	12 hours	24 hours	48 hours	Discharge	7 days	30 days	90 days	
Enrolment											
Eligibility screen	x										
PIS given	x										
Informed consent	x										
Registration	x										
Allocation		x									
Intervention											
GDFT (intervention)										
Standard care (control)										
Assessments											
NICOM monitoring											
Blood tests			x	x	x	x					
HRQoL			x					x	x	x	x
Complications			x	x	x	x	x		x	x	x
Other outcomes			x	x	x	x	x		x	x	x

GDFT, goal-directed fluid therapy; HRQoL, health-related quality of life; NICOM, non-invasive cardiac output monitoring; PIS, patient information sheet.

### Participants

Adults (>16 years) admitted as an emergency with acute pancreatitis will be included. Acute pancreatitis must be confirmed by the international consensus criteria (box 1).^19^ The exclusion criteria will be patients transferred for the management of complications of acute pancreatitis, requiring immediate admission to the ICU, chronic pancreatitis in whom an acute exacerbation cannot be confirmed, a history of cardiac failure in the past 3 months and those unable to provide fully informed consent.

Box 1International consensus criteria for acute pancreatitisAcute pancreatitis diagnosis confirmed with two of the following three features:Abdominal pain consistent with acute pancreatitis (acute onset of a persistent, severe, epigastric pain often radiating to the back).Serum amylase or lipase activity at least three times greater than the upper limit of normal.Characteristic findings of acute pancreatitis on contrast-enhanced CT (CECT) and less commonly MRI or transabdominal ultrasonography.

### Recruitment

Patients referred from the emergency department for admission through the emergency surgical team will be screened by the general surgical registrar on call. Due to the time-dependant nature of this trial, similar to most trauma and emergency surgery studies, a summarised and abbreviated patient information sheet will be provided for patients initially on arrival and they will be subsequently provided with an in-depth version. Informed consent will be obtained by a member of the clinical or research team trained in Good Clinical Practice.^20^ The trial nursing staff responsible for instituting the trial intervention will be contacted within 4 hours of diagnosis. Intervention or standard of care will commence within 6 hours of the diagnosis for the next 48 hours of inpatient stay. Since the primary goal of this study is to assess the feasibility of delivering *ward-based* GDFT, patients requiring escalation of care and admission to ICU during the intervention will only have continued cardiac output monitoring until completion of the 48 hours’ period.

### Randomisation

This will be performed using ‘Sealed Envelope’, an internet-based randomisation system (www.sealedenvolpe.com). Eligible patients who have consented to take part in the trial will be 1:1 randomised to ward-based GDFT or standard care, stratified by site on admission, prior to ward transfer. The trial research nurse responsible (unblinded) will log into the database and create randomisation codes for both groups online. Information on randomisation will be stored in the case report form (CRF).

### Intervention

GDFT will be carried out for 48 hours. It can take up to 48 hours for the severity of pancreatitis to manifest and is considered the ‘golden’ period for interventions that may decrease severity.^21^ GDFT will be based on a standard algorithm which uses the SV derived from non-invasive cardiac output monitoring (NICOM) using the Cheetah NICOM (figure 2). The fluid administration regimen will be as follows: maintenance fluid should be administered at 1.5 mL/kg/hour (based on ideal body weight) using a balanced crystalloid solution to be ensured that a regulated volume of fluid was given per hour in order to avoid fluid overload in this group. Previous studies have been criticised for excessive maintenance fluid prescribed in the GDFT group.^22^ It was also felt that placing restrictions on the maintenance fluid prescription may influence decision-making in this group and affect the enthusiasm for clinicians to agree in patients participating in the study.

**Figure 2 F2:**
[figure not shown]
Goal-directed fluid therapy (intervention) protocol. Flow diagram of SV optimisation with maintenance fluid administration. Patients randomised to goal-directed fluid therapy (GDFT) will receive a 1.5 mL/kg/hour of intravenous crystalloid maintenance fluid and four hourly visits from the trial nurses. At the first 4-hour visit, a bolus of 250 mL crystalloid over 5–10 min will be administered. An SV rise of >10% would indicate fluid responsiveness and a further cycle of fluid bolus is administered until there is no SV rise >10%. At the next four hourly visits if SV has dropped by >10% the cycle is repeated. SV, stroke volume.

On admission SV is recorded and an initial bolus of 250 mL of intravenous fluid (balanced electrolyte solution) is given over 5–10 min. If there is a sustained rise in SV of greater than 10% for 15 min or more, this indicates fluid responsiveness and a repeat 250 mL bolus will be given. If there is not a rise in SV of greater than 10% then the patient is deemed fluid unresponsive and no further fluid boluses are administered. SV monitoring continues four hourly and if it decreases by more than 10% a further fluid bolus is administered as above.

### Control (standard care group)

The choice of fluid type, volume and rate of administration on the first 48 hours of admission for patients randomised to the control arm will be decided by the clinical team caring for the patient in order to mimic a real-world situation. Cardiac output monitoring variables will be measured every 4 hours on the standard care arm during the first 48 hours, however, the results will be blinded to the clinical team. The choice of fluid type, volume and rate will be recorded in detail. All other clinical, biochemical and HRQoL outcome measures will also be recorded for standard of care patients as outlined in the ‘outcome measures’ section.

The Cheetah NICOM device (Cheetah Medical) is a CE (*C*
*onformité*
*E*
*uropéene*) marked device which has been purchased for this study and training has been arranged for all staff on the equipment and the associated fluid administration algorithm which will be a key component of the trial. The research team will follow hospital policy on signals for ICU outreach reviews and escalation of care to ICU. NICOM monitoring and outcome measures will be recorded in ICU for both control and GDFT arms.

### Blinding

It will not be possible to blind the research or clinical team during the first 48 hours of the study. However, the participants, outcome assessors of HRQoL and statisticians will be blinded to the groups. Patient blinding will be aided by NICOM monitoring of both intervention and control groups but performing GDFT in the intervention group alone. NICOM data from the control group will be collected at the same time points as the intervention group and will not be available to the treating clinicians.

### Outcome measures

The primary outcome of the trial will be an assessment of feasibility. In particular, the ability to identify and recruit patients at the selected sites to a study of acute pancreatitis. A recruitment rate of at least 30% over 17-month trial period will be deemed as successful. We will also assess the availability of study team for a condition presenting as an emergency, ability to randomise and commence ward GDFT within 6 hours of admission, completion rate of 48 hours of GDFT, rate of withdrawal (less than 20%) from GDFT protocol, reasons for withdrawal from GDFT protocol and proportion of complications in the two groups. Although the study is not powered to show differences in haemodynamic variables, we will analyse the haemodynamic data (such as SV and CO) at the end of the trial for patients in both groups to, at least, be able to conclude that we have optimised SV status of patients correctly according to the GDFT protocol drawn at the start of the trial. These data will be presented along with the main feasibility endpoints.

Several secondary clinical, surgical, biochemical, safety and quality of life outcomes will also be collected. Mortality will be assessed as well. Clinical outcomes will include severity of pancreatitis as assessed by Glasgow score, proportion of patients with severe acute pancreatitis, necrotising pancreatitis, infected pancreatic necrosis, requiring ITU stay, requiring renal replacement therapy, requiring ventilation, requiring surgical interventions for complications related to pancreatitis and incidence of positive blood cultures. Resource use data for health economic analysis on length of hospital stay, length of ICU stay, and number of days ventilated, time to return to pre-pancreatitis activities, number of workdays lost (in those who work) and costs (NHS and personal social services perspectives) will be collected. HRQoL will be assessed using the well-validated EuroQol-5 Dimension (EQ-5D) questionnaire on admission as baseline and subsequently on days 7, 30 and 90. All complications of pancreatitis including treatment-related adverse events (postradiological and surgical complications as classified by Clavien-Dindo Classification) and serious adverse events related to intervention will be recorded up to discharge and at follow-up. Routine biochemical tests performed as part of clinical care including blood gases, liver function tests, clotting profile, renal function, amylase, full blood count and C-reactive protein (CRP) will be recorded on admission and daily up to 2 weeks and biweekly up to discharge. In addition, serum samples will be collected from participants in both groups on admission, 12, 24 and 48 hours’ time points and stored at −80° for future analysis of biomarkers in acute pancreatitis.

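### SV and CO values from the two groups cannot show that the bolus algorithm was followed, and the protocol defines no step-level adherence measure that could

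*Protocol article*

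**What the plan says.** The Abstract (Introduction) lists among the trial's purposes "adherence to a GDFT protocol, safety, participant withdrawal", so adherence is named separately from withdrawal.

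Outcome measures then gives the one analysis aimed at correct delivery: "we will analyse the haemodynamic data (such as SV and CO) at the end of the trial for patients in both groups", so as to "conclude that we have optimised SV status of patients correctly according to the GDFT protocol". The same sentence opens with a caveat, "Although the study is not powered to show differences in haemodynamic variables", and the next says these data will be shown beside the main feasibility endpoints.

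The Intervention section and the Figure 2 legend define the algorithm as rules applied patient by patient. A 250 mL bolus is given and repeated if SV rises by more than 10%. "If there is not a rise in SV of greater than 10% then the patient is deemed fluid unresponsive", and boluses stop. After that, "SV monitoring continues four hourly and if it decreases by more than 10% a further fluid bolus is administered as above".

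Other delivery measures are given under Outcome measures, Data collection and analysis, Assessment of feasibility, and Progress to full trial: start within 6 hours, completion of 48 hours, rate of withdrawal from the GDFT protocol (target below 20%, reported with a 95% CI) with reasons, logged failures to commence, and a progression criterion of at least 80% of those randomised to GDFT.

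**The concern.** Whether a protocol of this kind was followed is a question about actions: was the check done, was a bolus given when the rule called for one, and was it withheld when the rule did not. SV and CO are physiological results. They depend on the actions, but also on how responsive the patient is and, in any contrast between groups, on what the control clinicians chose to do.

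A feasibility trial exists partly to show that the intervention can be delivered as designed. If it reports from SV and CO that delivery was correct, the case for a definitive trial would include a fidelity claim that its data do not support. Poor fidelity, which a later trial would need to know about, could go unseen in patients who complete 48 hours without withdrawing.

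**Working it through.** The document gives no figure for SV, CO or adherence, so there is none to reproduce. The check is one of logic, with arithmetic as illustration.

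**1. Do SV values identify adherence?** Set the rules beside the intended conclusion.

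- *Followed, no SV rise.* A patient found fluid unresponsive correctly receives no further bolus. Adherence is complete and SV is flat.
- *Not followed, SV rises.* Boluses given without a trigger, or after missed checks, can still raise SV.
- *Not delivered, SV still recorded.* Under Recruitment, patients escalated to ICU have monitoring only. Under Control (standard care group), NICOM is recorded in ICU for both arms. GDFT-arm SV data can therefore include periods with no GDFT.
- *No fixed reference.* Control fluids are at the clinical team's discretion, so control SV is not a benchmark for correct delivery.

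The first two points apply equally to a trend within patients if SV is read without the matching bolus record.

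**2. Illustration for a group contrast.** Assume full delivery raises mean SV by g = 1 SD, adherence is a, and control clinicians achieve a share c of the same gain. The expected difference is g × (a − c).

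| Adherence a | Control share c | Expected difference | Simulated share of trials significant (25 per arm, two-sided 5%) |
|---|---|---|---|
| 1.0 | 0 | 1.0 SD | 94% |
| 1.0 | 0.5 | 0.5 SD | 43% |
| 0.5 | 0 | 0.5 SD | 42% |
| 1.0 | 1.0 | 0 | 5% |

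The second and third rows cannot be told apart, although adherence is 100% in one and 50% in the other. The fourth shows perfect adherence with no difference. A larger sample would not help, because the expected values themselves coincide.

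**3. Precision of a group contrast.** With 25 per arm, the 95% half-width for a difference in means of one unadjusted measurement is 1.96 × √(2/25) = 0.55 SD. This agrees with the protocol's own statement that it lacks power here. The argument in step 1 does not depend on it.

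**4. What a direct measure would deliver.** Visits at 0, 4, …, 48 hours make 13 per patient, and 25 × 13 = 325. Counting from 4 hours gives 25 × 12 = 300. Score one decision per visit, assume 85% adherence, and inflate the variance by 1 + (13 − 1) × ICC:

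| Assumed ICC | Design effect | Effective n (325 / design effect) | 95% half-width, 1.96 × √(0.85 × 0.15 / effective n) |
|---|---|---|---|
| 0.1 | 2.2 | 148 | 5.8 points |
| 0.3 | 4.6 | 71 | 8.3 points |
| 0.5 | 7.0 | 46 | 10.3 points |

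These are best cases, because patients moved to ICU contribute fewer ward decisions.

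**5. Can decisions be scored from the text as it stands?** Not yet. The Figure 2 legend puts the first bolus at the first 4-hour visit; the Intervention text puts it on admission. The legend needs an SV rise above 10%; the text needs that rise sustained for 15 minutes or more. A rise above 10% that does not last 15 minutes would make a repeat bolus correct under one description and incorrect under the other.

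**The case against.** Four objections carry weight.

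- *No between-group test is named.* A reader might infer that the plan rests fidelity on a formal group comparison. The text says only that data from both groups will be analysed, and it disclaims power for differences. That makes a contrast the natural reading but does not state one. The four-hourly SV series could also serve a check within patients. This stands, so the point is worded to cover both readings: without the bolus actions, neither supports the stated conclusion.
- *Adherence is already measured.* A reader might infer that adherence has no valid measure at all. The document does not support that: the 6-hour start, 48-hour completion, withdrawal and the 80% criterion are sound measures of initiation and persistence. Only bolus-by-bolus fidelity lacks a defined measure.
- *The article is condensed and the SAP is not shown.* A step-level variable may be defined there, and its absence alone would be no finding. What stands against the article is the inference it states, which unseen detail would not make valid.
- *The consequence is limited.* SV and CO appear in no progression criterion, and Data collection and analysis labels everything except recruitment and withdrawal rates as exploratory. This limits the harm. It does not sit well, though, with a plan to conclude that delivery was correct and to present the data with the main endpoints.

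It is also tempting to turn the 0.55 SD half-width into a percentage of mean SV and set it against the algorithm's 10% step. That should not be done. One is uncertainty in a mean between patients and the other a trigger within a patient, and the documents give no SD for SV.

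**Conclusion.** The concern holds in a limited form. SV and CO values cannot, by themselves, justify concluding that SV was optimised correctly according to the GDFT protocol. The document measures whether GDFT was started and continued, but it defines no measure of whether the bolus algorithm was obeyed, despite naming adherence as an aim.

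The logical part rests only on the document's own rules. The 0.5 SD coincidence rests on an assumed 1 SD gain and assumed control shares. The precision of the alternative, about ±6 to ±10 points, rests on assumed 85% adherence, an ICC of 0.1 to 0.5 and up to 325 decisions. The change is a worthwhile, inexpensive improvement. The finding does not undermine the trial's recruitment, completion or withdrawal results.

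**What to change.** 1. In the GDFT arm, for time on the ward, add two feasibility outcomes: (a) four-hourly assessments done divided by those due; (b) bolus decisions matching the algorithm (given when triggered, withheld when not) divided by all decisions. Give (b) a 95% CI clustered by patient.
2. Keep SV and CO in both groups as descriptive data, and remove from them the conclusion about correct delivery.
3. Before scoring, have the sponsor reconcile the Figure 2 legend with the Intervention text on the timing of the first bolus and on whether the SV rise must be sustained. Which description applies is for the clinical team.
4. Confirm that bolus times are recorded in the GDFT arm. The article states detailed recording of fluid type, volume and rate only in the control section.

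The cost is some extra coding and the confirmation of bolus recording. The four-hourly SV readings are already planned. If bolus times are not captured in the GDFT arm, a field for them would have to be added to the case report form.
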